**Fig. 2 Fig2:**
[figure not shown]
Participant flow diagram across clinic and community-based study components

This mixed-methods design allows for a more complete understanding of non-surgical management than quantitative or qualitative approaches alone, [62] emphasizing our primary outcome of effectiveness via robust assessment of clinical and patient-reported outcomes, and providing important acceptability and cost burden data to inform future implementation. Our approach maintains a focus on rapid translational gains for clinical intervention and useful information for key decision-makers.

### Study setting

Participants will be recruited from four facilities in Ghana and Kenya. In Ghana, the study will enroll participants at Mercy Women’s Catholic Hospital in Mankessim and Tamale Fistula Centre at Tamale Central Hospital in Tamale. In Kenya, the study will enroll participants at the Gynocare Women’s and Fistula Hospital in Eldoret and WADADIA-Habibat Mother and Child Holistic Health and Training Hospital in Malindi.

### Stakeholder engagement

Trial implementation and interpretation will be supported by a Community Advisory Board and the Ghana and Kenya National Fistula Task Forces. The Community Advisory Board (CAB; *n* = 5–8) will provide input on recruitment, study procedures, findings, and interpretation to increase community engagement and improve research quality. An effort will be made to include board members who are involved in clinical operations and can provide some institutional perspective. Other CAB members may represent social organizations where this intervention could be implemented, such as community-based organizations with fistula programming. Others will represent strategic regional and national fistula organizations.

### Study population and sample size

#### Quantitative

We will recruit up to 100 women with VVF to participate in the quantitative study activities (Aims 1–3). Study participation will not delay time to surgery for study participants through careful planning of recruitment efforts in alignment with timelines of surgical availability and through early study exit from community-based activities if surgery becomes available sooner. Our sample size calculation is not dependent on balance between study sites, thus the breakdown of participants by study site is not pre-defined but will depend on recruitment activities. Detailed inclusion and exclusion criteria are as follows:

*Inclusion criteria*: VVF confirmed by dye test and clinical exam at least three centimeters (cm) from the external urethral orifice regardless of size, adequate vaginal capacity to accommodate the cup (per physician), willing to insert and remove cup/cup+, clear understanding of the study procedures and willing to participate fully, not yet undergone surgical fistula repair or previously failed surgical repair, at least 6mo post-surgery if previous fistula repair, ≥3months post-delivery if recent birth, age 18 + or emancipated minor per Ghanaian or Kenyan law, and ability to speak English or local language.*Exclusion criteria*: Presence of any rectovaginal fistula (i.e., alone or in combination with VVF); not able to provide informed consent (e.g., incapacitated); does not leak more than 6 ml over 6 h during screening examination; and fistulas deemed curable via prolonged catheterization. Pregnant individuals will not be excluded from the study participation if they meet the inclusion criteria specified above. Pregnant or menstruating women will not be excluded and their experiences and outcomes will be compared to the larger sample.

Cross-over trial designs provide greater efficiency than parallel designs due to within-subject treatment comparisons where each subject serves as their own control, resulting in lower sample size requirements for statistical power. Our sample size of up to 100 participants (400 observations) is calculated to assess: (1) a ≥ 65% reduction at six hours in observed urinary leakage, and (2) a mean 40% quality of life difference at three months between the cup and cup+ (measure range 0-100; Supplementary Figures). We expect > 80% retention over three months study follow-up based on our research with 12-months follow-up with 98% retention with this target population in Uganda^63^ and 3-months follow-up in Ghana with 84% retention, [64, 65] and have inflated our target sample size conservatively.

#### Observed leakage

Minimum difference was estimated from our efficacy study plus expert clinical opinion as the minimum clinically significant leakage reduction from pad test [24]. Analytical sample size was calculated at 50 using an ANCOVA model with a 2-tailed, alpha error = 0.025 to obtain statistical power of 0.8–0.9.

#### Quality of life

Using dependent t-test with 2-tailed, alpha error = 0.05, estimated mean difference of effect between the cup and cup + of 40%, and power 0.85 to avoid type 1 error, required sample size is 59. Estimates of the effect are based on data collected within a longitudinal study of post-surgical fistula repair patients in Uganda, [66] wherein participants were asked about quality of life using the post-repair fistula reintegration measure which is standardized to a range of 0-100 [67]. Participants reported a mean of 36.7 (SD = 19.0) at the time of fistula repair (referring to living with fistula) and a mean of 78.0 (SD = 22.7) at follow up (6 months post-repair), reflecting a mean change of 40.5 (SD 28.1): 54.2 (SD 14.5) among those who were not leaking urine and 13.1 (SD 28.9) among those who continued leaking urine. The cup + is estimated to have a comparable improvement on quality of life as surgical repair, while the cup, based on our observations during our feasibility study [37] and on expert opinion, is estimated to have a smaller effect on quality of life over the long-term (3 months) as it has 1/15th of the capacity for urine storage and thus will need more frequent emptying than the cup+.

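### The quality-of-life sample size of 59 does not follow from a 40-point difference on the 0-100 scale; it matches a standardised paired effect of about 0.40, which the article never states.

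*Protocol article*

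**What the plan says.** The opening sample-size text (Study population and sample size, Quantitative) gives two bases for the target of up to 100 women. The second is "a mean 40% quality of life difference at three months between the cup and cup+ (measure range 0-100; Supplementary Figures".

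The Quality of life paragraph of the same section supplies the calculation. The test and error rate are "Using dependent t-test with 2-tailed, alpha error = 0.05", and the result is given for a difference "between the cup and cup + of 40%, and power 0.85 to avoid type 1 error, required sample size is 59". (Power guards against type II error, not type I; this is a slip of wording.)

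The effect is drawn from a cohort followed after fistula surgery. The article gives a mean of 36.7 (SD 19.0) before repair and 78.0 (SD 22.7) six months after, "reflecting a mean change of 40.5 (SD 28.1"). It splits the change into "54.2 (SD 14.5) among those who were not leaking urine" and 13.1 (SD 28.9) among those still leaking. Cup+ is expected to do about as well as surgery, and the cup less well.

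No standardised effect is given, and no SD for the difference between cup and cup+.

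**The concern.** The test, alpha, power, effect and resulting n are all printed, so the calculation can be checked. The natural reading of 40% on a 0-100 measure is 40 points. The source data point the same way: the overall change is 40.5, and the dry and still-leaking groups differ by 54.2 - 13.1 = 41.1. A difference that large against SDs below 30 needs very few pairs, so 59 looks out of place.

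This is one of the two stated bases for the size of the trial. If cup and cup+ do not differ at three months, readers will judge that result against the difference the trial says it was sized for. If 59 belongs to a much smaller difference, the stated benchmark is wrong.

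**Working it through.** **Inputs.** From the Quality of life paragraph: paired t-test, two-sided alpha 0.05, power 0.85, difference 40%, SDs of 14.5, 19.0, 22.7, 28.1 and 28.9. The SD of the paired difference is not given.

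**Formula.** With standardised effect d = mean difference / SD of the difference, power at n pairs comes from the noncentral t distribution with n - 1 degrees of freedom and noncentrality d × √n. The required n is the smallest that reaches 0.85.

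**Step 1: what reproduces 59.** With d = 0.40, power is 0.8496 at 58 pairs and 0.8557 at 59, so n = 59 exactly. Any d from about 0.397 to 0.400 gives the same answer.

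**Step 2: 40 points.**

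| SD of the difference | d = 40/SD | Pairs needed |
|---|---|---|
| 14.5 | 2.76 | 4 |
| 19.0 | 2.11 | 5 |
| 22.7 | 1.76 | 6 |
| 28.1 | 1.42 | 7 |
| 28.9 | 1.38 | 7 |
| 39.7 (assumed) | 1.01 | 11 |

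The last row assumes two uncorrelated changes with SD 28.1 each: √(28.1² + 28.1²) = 39.7. The two change-score subgroup SDs (14.5 and 28.9) bound the quoted change-score range, giving 4 to 7 pairs.

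**Step 3: could an unstated SD rescue 40 points?** For 40 points to need 59 pairs, the SD of the difference must be about 40/0.397 = 101. The difference between one woman's two scores on a 0-100 scale lies between -100 and 100. With mean 40, its SD cannot exceed √(100² - 40²) = 91.7. No admissible SD gives 59.

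**Step 4: relative readings of 40%.**
- 40% of the 36.7 baseline is 14.7 points: 35 pairs at SD 28.1.
- 40% of the 40.5 change is 16.2 points: 29 pairs at SD 28.1. With uncorrelated changes it is 56 (SD 28.1 each, SD of difference 39.7), 58 (28.1 and 28.9, 40.3) or 60 (28.9 each, 40.9).

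**Step 5: d = 0.40 in points.** 0.40 × 28.1 = 11.2 points; 0.40 × 39.7 = 15.9 points. The ratio of 40 to the implied difference is 40/11.24 = 3.6 at SD 28.1. It runs from 2.5 (SD 39.7) to 6.9 (SD 14.5).

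**Step 6: the home phase.** Under Community-based procedures each woman is individually randomised to one device for home use, so the three-month comparison is between two arms. Assume 100 enrolled, 80% retained and 1:1 allocation: 100 × 0.80 / 2 = 40 per arm. A two-sample t-test with 40 per arm has noncentrality d × √(40/2). It reaches 85% power at d = 0.68, and 0.68 × 28.1 = 19 points. Its power at d = 0.40 is 0.42; 114 per arm would be needed for 85%.

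**The case against.** **The 40% may be relative.** The article speaks of a difference in effect and expects the cup to do less well than cup+. A reader could take this as 40% of the 40.5-point surgical change, 16.2 points. With uncorrelated changes that gives 56, 58 or 60 pairs, which bracket 59 without hitting it. This stands as a live alternative. It would mean that 59 belongs to about 16 points, and the text would still need correcting, because the article places the 40% beside a 0-100 range and does not say what it is a percentage of.

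**What was entered is unknown.** A reader might infer from the exact match that 0.40 was typed in as an effect size, that the trial was therefore sized for 11 points, and that the stated difference is wrong by a factor of 3.6. The documents do not support stating this as fact. They give no standardised effect. SD 28.1 describes change after surgery and is not the SD of a between-device difference. The Supplementary Figures the article cites are not shown. The factor is 3.6 only at SD 28.1.

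**No shortage for 40 points.** A reader might also infer that the trial is too small for its stated difference. It is not: under the stated test 59 far exceeds the 4 to 11 pairs required, and even in a two-arm comparison at SD 28.1, 40 points would need only 10 per arm.

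**Paired versus parallel is a separate matter.** This is fair. Step 6 adds nothing to the evidence that 59 and 40 points disagree. It belongs in the correction because a restated paired figure would still not describe the comparison the home phase makes.

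**Conclusion.** The point holds as a mismatch between printed inputs and printed result. Under the stated test, alpha and power, no possible SD makes 40 points on the 0-100 scale require 59 pairs. That conclusion needs no assumption beyond reading 40% as 40 points.

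The figure corresponds to a standardised paired effect of about 0.40. In points this is about 11 if the SD of the difference is 28.1 and about 16 if it is about 40. Which inputs were used cannot be settled from the article.

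The consequence is for interpretation. The difference the article says it was sized for is not the one 59 corresponds to, so a null cup versus cup+ result would be read against the wrong benchmark. The home-phase figures (19 points at 85% power; 42% power for 0.40 SD) hold only for about 40 completers per arm, and the 19 points also needs SD 28.1.

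**What to change.** In both sample-size passages (the opening text under Quantitative and the Quality of life paragraph):

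1. State the three inputs that produce 59: the difference in points, the SD of the paired difference and the resulting standardised effect. The investigators must supply these from their own calculation.
2. Do not call it a 40% difference on the 0-100 scale unless those inputs support it. If the percentage is relative, say what it is a percentage of.
3. Add the difference that the individually randomised home phase can detect, with its assumptions. With 100 enrolled, 80% retained and 1:1 allocation, this is about 0.68 SD at 85% power (about 19 points at SD 28.1), with about 42% power for 0.40 SD.
4. Correct the phrase that ties power to type I error.

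The cost is a rewritten paragraph. No extra participants are needed.

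### The quality-of-life sample size of 59 matches a paired standardised effect of 0.40, not a 40-point difference, and the paired test does not fit the two-arm home phase, so the stated 85% power describes neither

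*Protocol article*

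**What the plan says.** All references are to the protocol article.

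- **Study population and sample size, Quantitative.** Up to 100 women are to be enrolled, with more than 80% expected to be retained at three months. One of the two targets behind this number is "a mean 40% quality of life difference at three months between the cup and cup+ (measure range 0-100").
- **Study population and sample size, Quality of life.** The method is given as "Using dependent t-test with 2-tailed, alpha error = 0.05", with a 40% difference between the devices and "power 0.85 to avoid type 1 error, required sample size is 59". (Power guards against a type II error, so the wording is also a slip.) The supporting data come from surgical repair patients and are in scale points: a "mean of 36.7 (SD = 19.0) at the time of fistula repair", 78.0 (SD 22.7) six months later, and a mean change of 40.5 (SD 28.1). By leakage status, the change was "54.2 (SD 14.5) among those who were not leaking urine and 13.1 (SD 28.9) among those who continued leaking urine". Cup+ is expected to do about as well as surgery, and the cup less well.
- **Community-based procedures.** On the last clinic day each woman is individually randomised to take home one device, cup or cup+.
- **Table 2.** Quality of life is recorded at 0 h and at months 1, 2 and 3. It is not recorded in the clinic crossover periods.
- **Data analysis, Quality of life.** Cup and cup+ are to be compared on change in quality of life with a paired t-test.

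**The concern.** The effect is described as 40% on a 0-100 measure and supported only by data in points. A 40-point gap against SDs of 14.5 to 28.9 is so large that a handful of women would show it, so 59 looks far too many for the effect described. Separately, a dependent t-test needs two scores per woman, one under each device, and the home phase yields only one device per woman.

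What is at stake is how the cup versus cup+ quality-of-life result will be read. If the trial finds no difference, a reader will rely on the stated 85%, and that percentage has to belong to the effect and the design actually in use.

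**Working it through.** **Inputs.** Two-sided alpha 0.05, power 0.85, n = 59 and the SDs 19.0, 22.7, 28.1, 14.5 and 28.9 are from the sample size section. Pooling the two leakage-status SDs with equal weight gives √((14.5² + 28.9²)/2) = 22.9. Allocation at home is assumed 1:1, as no ratio is stated. Retention of 80% of 100 gives 80 completers, about 40 per arm.

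**Formulas (exact, non-central t).** Paired: n − 1 degrees of freedom, non-centrality dz·√n, where dz is the mean difference divided by the SD of the differences. Two-sample: n₁ + n₂ − 2 degrees of freedom, non-centrality d·√(n₁n₂/(n₁ + n₂)). Power is the probability of exceeding the two-sided 5% critical value.

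**Step 1: reproduce the 59.** With dz = 0.40, power is 84.96% at n = 58 and 85.57% at n = 59, so 59 is the smallest n that reaches 85%. Working back, n = 59 requires dz between 0.397 and 0.400.

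**Step 2: try 40 points instead.** The paired column takes each quoted SD as the SD of the within-woman differences.

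| SD | 40/SD | Pairs for 85% | Women per arm for 85% |
|---|---|---|---|
| 14.5 | 2.76 | 4 | 4 |
| 19.0 | 2.11 | 5 | 6 |
| 22.9 | 1.75 | 6 | 7 |
| 28.1 | 1.42 | 7 | 10 |
| 28.9 | 1.38 | 7 | 11 |

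With the overall SD of change (28.1), 7 pairs suffice. Across 22.9 to 28.9, two arms need 7 to 11 women each. To obtain 59 pairs from 40 points, the SD of the paired differences would have to be about 40/0.40 = 100. Differences between two 0-100 scores lie between −100 and 100. With mean 40, their SD cannot exceed √((100 − 40)(40 + 100)) = √8400 ≈ 92. So the stated n cannot come from a 40-point difference under the stated test.

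**Step 3: what 0.40 SD is in points.** 0.40 × 19.0 = 7.6 and 0.40 × 28.9 = 11.6, so about 8 to 12 points rather than 40.

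**Step 4: the design.** One device per woman at home, and no quality-of-life score during the clinic crossover, leave no within-woman cup versus cup+ difference. The comparison is between two independent groups.

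**Step 5: power in two parallel arms (unadjusted, one time point).**

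| Women analysed | 0.40 SD | 40 points, SD 28.9 |
|---|---|---|
| 59 (29/30) | 33% | above 99.9% |
| 80 (40/40) | 42% | above 99.9% |
| 100 (50/50) | 51% | above 99.9% |

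For 0.40 SD, 85% power needs 114 per arm: 228 evaluable, or 228/0.80 = 285 enrolled.

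**Step 6: what the planned enrolment delivers.** With 40 completers per arm, 85% power is reached at d = 0.678. That is 0.678 × 22.9 ≈ 15.5 points, or 0.678 × 28.1 ≈ 19 points.

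**The case against.** **The text says 40%, not 40 points, and other readings exist.** This stands in part. The points reading rests on the 0-100 range and the point-scale data, and the supplementary figures cited for the calculation are not shown. A relative reading, 40% of the 40.5-point change, is 16.2 points; with SD 28.9 a two-sample test then also gives 59, but per arm (118 in total) and not with the stated test, so it is probably a coincidence. A reader might infer that the document shows 40% being entered as Cohen's d. It does not: the exact match makes that the likely explanation, not a recorded fact.

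**The 41.1-point contrast is not the stated basis.** This stands. Because 54.2 − 13.1 = 41.1 is close to 40, a reader might infer that the plan assumes the cup does no better than failed surgery. The section reports both subgroup changes but never names their difference as the source of the 40%, and says only that the cup should have a smaller effect.

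**The harm is not one-sided.** This stands. For a true 40-point gap the trial has ample power even with 59 women in two arms.

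**The planned analysis is stronger than an unadjusted comparison at one visit.** This stands in part. A mixed model over the follow-up visits is planned. If follow-up scores correlated 0.5 with each other and 0.1 to 0.5 with baseline (assumed; no correlations are given), averaging three visits with baseline adjustment would give roughly 58 to 78% power for 0.40 SD at 40 per arm. That is still below 85%, and it concerns an average over three months, whereas the stated target is at three months.

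**The main effectiveness analysis is elsewhere.** This stands. The primary comparisons are placed on six-hour leakage, which this point does not touch.

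**Conclusion.** The concern holds in this form: the stated 85% power at n = 59 applies neither to a 40-point difference nor to the parallel home phase. It belongs to a paired comparison with a standardised effect of 0.40, and this design yields no such comparison.

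The two mismatches pull in opposite directions. It would be wrong to conclude that the trial is underpowered for the effect it describes, if that effect is 40 points. What can be said is that a difference of 0.40 SD, the effect that reproduces the 59, would be missed more often than not with 80 completers in an unadjusted comparison at one visit, and about half the time with 100.

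The mismatch between test and design does not depend on how the 40% is read, since the analysis section repeats the paired t-test. The power figures rest on 1:1 allocation, 80% retention of 100 women, and SDs borrowed from surgical repair patients. The correction concerns a stated power figure and one secondary comparison; randomisation, data collection and the leakage analysis stay as they are.

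**What to change.** 1. In the sample size section on quality of life, remove the 59 and the dependent t-test. State the target difference in scale points with the SD assumed for it, and say why that difference matters to patients. Correct the reference to type I error.
2. Add a statement for the actual design, for example: with up to 100 women randomised to home use and about 40 completers per arm, an unadjusted two-sample comparison at two-sided 0.05 has 85% power for a difference of 0.68 SD (about 15.5 points if the SD is 22.9, 19 points if it is 28.1); baseline adjustment lowers the detectable difference.
3. In the data analysis section on quality of life, replace the paired t-test for cup versus cup+ with a between-arm comparison adjusted for baseline, either ANCOVA at three months or the mixed model already planned with an arm-by-time term. Changing only the sample size section would leave the two sections in conflict.
4. Bring the cited supplementary figures into line with the new calculation.

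The cost is one rewritten paragraph, one changed sentence in the analysis section and, where needed, a revised figure. No further participants or measurements are required.

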#### Qualitative

Study staff will recruit ~ 30 trial participants, partners, and peers and ~ 20 providers (obstetrician-gynecologists, midwives/nurses, traditional birth attendants, community health workers). Participants will be targeted based on criterion purposive sampling to identify a diverse sample of those with high or low acceptability; high, low, or no subjective effectiveness, and severe or not severe stigma experiences. Each invited trial participant will be encouraged to invite one to two partners or peers to provide additional context. Final sample size will be determined by iterative appraisal of theme saturation as data are collected, [68] although a priori estimations suggest 20 to 30 participants will be sufficient. Interviews will seek to understand communication with partners and peers regarding fistula management decision making, context for fistula management decision making, adherence, cost, relationship dynamics, social support, and caregiver or courtesy stigma.

### Participant recruitment

#### Quantitative

Participants will be recruited from women accessing fistula repair services at study-engaged sites and through community outreach by trained nurses. Potential participants will undergo a two-stage informed consent process with trained study staff for communication of screening procedures, eligibility assessment and full study procedures. Women consenting to screening will undergo preliminary clinical examination by the site physician, a fistula surgeon, to determine eligibility. Potential participants will be informed that they will receive the treatment assignments in varying order across their clinic stay.

Eligible women will be guided through the consent process, invited to participate in the study, and enrolled if they agree. Participants receive up to ~$135 USD in Ghana and ~$100 in Kenya for the six days of screening, clinic use and observation, and home use, reflecting local clinic (travel time, lost wages during facility stay, expenses for childcare, and communications) and community-based (time and effort) costs. The total participation reimbursement each individual will receive is based on their sequential engagement in study activities (i.e., clinic-based, community-based, and in-depth interview), and has been carefully estimated based on local costs and approved by the local IRBs. Participant transportation to the clinic and clinic-based expenses (e.g., food, water, bedding) are provided by the study.

